## Abstract

**Background:**

More than half of infants with complex congenital heart disease (CHD) will have a neurodevelopmental disorder of multifactorial causes. The preoperative period represents a time-window during which neonates with complex CHD are in a state of hypoxia and hemodynamic instability, which fosters the emergence of brain injuries and, thus, affects early brain networks and neurodevelopmental outcomes. Currently, there is no consensus regarding the optimal age for cardiac surgery in terms of neurodevelopmental outcomes, and its definition is a real challenge. Our aim is to determine the relationship between cardiac surgical timing and long-term neurodevelopmental outcomes for various types of complex CHD.

**Methods:**

We hypothesize that earlier surgical timing could represent a neuroprotective strategy that reduces perioperative white matter injuries (WMIs) and postoperative morbidity, leading to improved neurodevelopmental outcomes in infants with complex CHD. Firstly, our prospective study will allow us to determine the correlation between age at the time of surgery (days of life) and neurodevelopmental outcomes at 24 months. We will then analyze the correlation between age at surgery and (i) the incidence of WMIs (through pre- and postoperative MRIs), (ii) postoperative morbidity, and (iii) the duration of the hospital stay.

**Implications and Dissemination:**

This research protocol was registered in the Clinical Trial Registry (National Clinical Trial: NCT04733378). This project aims to help launch the first Neurocardiac Investigation Clinic in Marseille — AP-HM — to propose an overall personalized monitoring and treatment program for patients operated on for complex CHD.

## Introduction

1.

Congenital heart disease (CHD) is the most common birth defect, affecting 9 neonates out of every 1,000 live births (i.e., nearly 1% of births) (1). Half of these children have complex CHD requiring cardiac surgery during the first months of life (1). Additionally, more than 50% of them have a neurodevelopmental disorder resulting from multiple additive, collinear, and interacting risk factors, including genetic variants, parental education, fetal circulatory disorders, intraoperative factors, and postoperative complications (2). The current prognosis for neonates with complex CHD warrants the development of prevention strategies aimed at improving their neurodevelopment outcomes and, thus, their quality of life. Cardiac surgery with its intrinsic risk factors, such as the duration of extracorporeal circulation (EC) or the realization of circulatory arrest, does not determine the neurodevelopmental outcomes of these patients. Indeed, the preoperative period represents a window of time during which neonates with complex CHD are in a state of hypoxia and hemodynamic instability, fostering the emergence of brain injuries (3–5) and, thus, affecting early brain networks (6) and neurodevelopmental outcomes.

For patients with TGA (Transposition of Great Arteries) or HLHS (Hypoplastic Left Heart Syndrome), later cardiac surgery leads to a higher incidence of white matter injuries (WMI) (7, 8), which is a well-known prognostic factor for motor (9–12), language (11), and cognitive (10, 12, 13) impairment, as well as behavioral issues (14). Additionally, Anderson et al. (15) demonstrated that conducting the arterial switch operation (ASO) on neonates with TGA before the third day of life reduced the major postoperative morbidity of these patients in terms of neurological (occurrence of seizures, ischemic stroke), cardiological, and infection complications. Patients with left ventricle hypoplasia operated on later in the neonatal period also presented higher postoperative morbidity (16). Similarly, patients with TGA given the ASO after 2 weeks of life experienced impaired perioperative brain growth and slowed language development (17). Conversely, a major hypotrophy (weight < third percentile) or hemodynamic instability can delay the surgery, which may then be considered too risky. The fetal, pre and intraoperative risk factors of brain injuries are listed in the Table 1. All postoperative morbidities (Table 2) are deemed as potential risk factors for brain injuries.

**Table 1 T1:** Foetal and preoperative risk factors of brain injuries.

	Foetal period	Preoperative period	Intraoperative period
Risk Factors of Brain injuries	Gestational Age	Postnatal diagnosis	CPB duration (min)
	IUGR	Lower arterial oxygen saturation	Aortic clamp time (min)
	Brain volume	Lower apgar scores at 5 min	DHCA (min)
			Selective cerebral perfusion (min)
	Brain immaturity	Abnormal aEEG background pattern	Low Flow
		Longer time to surgery	
		Brain lactates	
		Low flow	
		Male sex	

CPB, Cardiopulmonary bypass; DHCA, Deep hypothermia with circulatory arrest; IUGR, Intrauterine growth restriction; aEEG, amplitude EEG.

**Table 2 T2:** Classification of post-op morbidities.

Morbidity category	Morbidities	
Cardiac / Respiratory	• Cardiac arrest, arrhythmias, JET • Low cardiac output syndrom • Extracorporeal membrane oxygenation • Post-op high-output failure • Re-intubation for acute respiratory distress	• Neonatal necrotizing enterocolitis • Systemic vein thrombosis • Acute renal deficiency with dialysis • Delayed sternal closure • Length of intensive care unit stay
Infectious	• Septicemia, fungemia • Infection of the surgical site, mediastinitis • Endocarditis	• Meningitis • Pneumonia
Neurological	• Ischemic cerebrovascular accident • Hemorrhagic cerebrovascular accident	• Epileptic seizure • Cerebral thrombophlebitis
Surgical	• Recurring diaphragmatic paralysis/paresis • Definitive AV block with device • Acute hemorrhaging requiring revision surgery	• Cardiac tamponade • Unplanned revision surgery • Chylothorax

There is no consensus regarding the optimal age for surgery in terms of morbidity and neurodevelopmental outcomes, and its definition is a real challenge. Importantly, at the present time, there are no established rules for determining the timing of surgery in our department. For the most common CHD types, the TGA are corrected during the first ten days of life. There is a more pronounced degree of variation for HLHS. This common practice won't be changed for our observational study.

Our aim is to determine the relationship between surgical timing and long-term neurodevelopmental outcomes for various types of complex CHD. Similarly to Anderson et al. (15) with postoperative morbidity, we aim to determine a cut-off point for surgical timing that will improve neurodevelopmental outcomes. For each type of CHD, we aim to determine a cut-off for surgical timing based on postoperative morbidity and neurodevelopmental outcomes. We hope that our findings will contribute to the development of surgical timing guidelines in the future.

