### Morbidities

2.9.

An analysis will be conducted for postoperative morbidities (see Table 2), including cardiac, hemodynamic, surgical, infectious, and neurological morbidities. Each of these complications will be analyzed independently.

Perioperative demographic and clinical data, including postoperative complications, will be collected retrospectively from prospectively completed medical files. We are particularly interested in the following data:
(i)demographic, including gender, education level, and economic status of the parents;(ii)preoperative, including whether there was a prenatal diagnosis of complex CHD, gestational age at birth, birth weight, head circumference at birth, Apgar score at 5 min, type of complex CHD, whether a Rashkind procedure was performed, the type of ventilation and its duration in days, hypotension requiring treatment, cardiac arrest, and arrhythmia.(iii)intraoperative, including age and weight at the time of surgery, hematocrit in the operating room, type of surgery, CPB time in minutes, selective cerebral perfusion time, and circulatory arrest time in deep hypothermia in minutes.(iv)postoperative, including ventilation (non-invasive, mechanical), duration in days, anesthesia, sedatives and exposure to antiepileptics, medication names and number of days used, and total and postoperative length of their stay in days.

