##### Morbidities

3.1.3.2.

The correlation between age at surgery (in number of days of life) and the occurrence of at least one of the elements of post-op morbidity (yes vs. no) will be assessed by describing and comparing age at surgery according to the presence and absence of a morbidity criterion. A comparison test for quantitative data will be used. The Student's t-test will be used if the application conditions are met; otherwise, the non-parametric Mann-Whitney test will be used. This analysis will be conducted with consideration for each element of morbidity in isolation.

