##### Length of hospitalization

3.1.3.3.

The correlation between age at surgery (in number of days of life) and the length of postoperative hospitalization will be assessed by estimating the Pearson's correlation coefficient with a 95% confidence interval if the application conditions are met (otherwise, the non-parametric Spearman's correlation coefficient will be estimated with a 95% confidence interval).

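### Table 2 puts ICU length of stay, a duration with no cut-off, into the yes/no morbidity endpoint; read literally, that endpoint has almost no comparison group

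*Protocol article*

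**What the plan says.** In the protocol article, Table 2 (section 1) carries the title "Classification of post-op morbidities". Its cardiac and respiratory row includes "Length of intensive care unit stay" beside items such as cardiac arrest and re-intubation. The entry has no number of days, no percentile and no qualifier marking the stay as long.

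Section 2.9 makes this table the analysed list: "An analysis will be conducted for postoperative morbidities (see Table 2), including cardiac, hemodynamic, surgical, infectious, and neurological morbidities". It adds: "Each of these complications will be analyzed independently".

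Section 3.1.3.2 defines the endpoint as "the occurrence of at least one of the elements of post-op morbidity (yes vs. no"). The method is "comparing age at surgery according to the presence and absence of a morbidity criterion", by Student's t-test or Mann-Whitney test. The section closes with: "This analysis will be conducted with consideration for each element of morbidity in isolation".

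Section 3.1.3.4 treats the morbidity element as a qualitative outcome in logistic regression, with the Firth correction as an option.

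Postoperative hospital stay is handled differently. In section 3.1.3.3, "the length of postoperative hospitalization will be assessed by estimating the Pearson's correlation coefficient", with Spearman's coefficient as the fallback, and section 3.1.3.4 gives it a linear model.

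**The concern.** A two-group test needs some infants with the outcome and some without. A length of stay has no absence unless a rule says which stays count, and the article gives no such rule. If any ICU stay counts as a morbidity, this one item decides the composite for almost every infant, whatever happens on the other elements.

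At stake is a secondary endpoint that feeds a stated aim: section 1 wants a surgical-timing cut-off for each type of heart disease, based partly on postoperative morbidity. An endpoint that cannot be computed as written invites a cut-off chosen once the data are known. That choice would set the composite rate and hence the comparison.

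**Working it through.** The article gives no event rate, effect size or power for the morbidity endpoint, so there is no stated figure to reproduce. The check is of the endpoint's logic, followed by its consequences at the planned size.

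**Inputs from the article**
- Planned cohort: 100 infants (sections 2.1 and 3.1.1), all having cardiac surgery with bypass in the first 2 months of life (section 2.1).
- Table 2 elements: 10 cardiac/respiratory + 5 infectious + 4 neurological + 6 surgical = 25. One is ICU length of stay, which leaves 24.
- ICU exposure: section 2.5.2 has patients admitted to the paediatric ICU after birth. No section states that every infant has a postoperative ICU stay.

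**Step 1: the composite.** Let p be the share of infants with any postoperative ICU stay. An infant is yes on the composite if yes on any element, so

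P(composite yes) ≥ p, and number in the no group ≤ 100 × (1 − p).

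- p = 1.00 gives 100 yes and 0 no. A t-test run with an empty group returns no statistic and no p-value.
- p = 0.99 gives at most 1 no.
- p = 0.95 gives at most 5 no.

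The other 24 elements can only shrink the no group further.

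**Step 2: the ICU-stay element alone.** The split is 100p against 100(1 − p). With p at or near 1 it has the same empty or near-empty group, and a logistic model has no contrast in its outcome to estimate. The Firth correction may return finite coefficients, but it cannot supply a missing outcome group.

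**Step 3: the other 24 elements alone.** Each is tested on its own occurrence, so none inherits the problem.

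**Step 4: with ICU stay removed.** The comparison then exists, and what it can detect depends on the composite rate from the remaining 24 elements. The article does not give that rate, so a range is assumed. The 5% two-sided alpha and 80% power are borrowed from section 3.1.1, which states them for the Bayley-IV correlation only.

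Detectable standardised difference in age = (1.960 + 0.842) × √(1/n_yes + 1/n_no)

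| Assumed yes / no | √(1/n_yes + 1/n_no) | Detectable difference (SD) | Power if true difference is 0.5 SD (assumed) |
|---|---|---|---|
| 50 / 50 | 0.200 | 0.56 | 71% |
| 70 / 30 | 0.218 | 0.61 | 63% |
| 80 / 20 | 0.250 | 0.70 | 52% |
| 90 / 10 | 0.333 | 0.93 | 32% |
| 95 / 5 | 0.459 | 1.29 | 19% |

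The last row is also the best case for the composite as written if 95% of infants have some ICU stay. The table shows why the rule has to be fixed in advance: moving the yes share from 50% to 90% raises the detectable difference from 0.56 to 0.93 SD.

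**The case against.** The strongest reply is that nobody would code any ICU stay as a complication. On this view the authors meant a prolonged stay or a continuous outcome, and the analysis plan will say which. The intention is plausible, but the article states neither reading. It does state the list, the yes/no rule and the test, and these do not fit together. This is a conflict inside stated rules, not a detail left out for brevity.

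A second reply is that the article never says every infant has a postoperative ICU stay. That is correct, and the 100-to-0 split is therefore an inference. The conclusion barely depends on it: 95% gives at most 5 infants in the no group, and the ICU-stay element still has no definition of yes.

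A third is that the scope is narrow. This stands: one composite and one of 25 elements are affected.

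A reader might also infer that the absence of death from Table 2 makes the comparison degenerate, or that early deaths bias the length-of-stay correlation by counting as short stays. The documents do not support either as a finding:
- Adding or omitting death does nothing to fill an empty no group, and a list of morbidities need not contain death.
- Section 2.3 excludes infants without the brain MRIs. Its wording is loose, but it may remove those who die before the postoperative scan.
- The article gives no mortality rate, no direction for any link between death and timing, and no time of death, so any size for such a bias would be assumed.
- Handling of deaths is commonly left to the full protocol or analysis plan.
- Giving deaths the worst rank would change the quantity estimated; it is a preference, not a correction.

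**Conclusion.** The point holds for ICU length of stay only. An unthresholded duration sits in a list that sections 2.9, 3.1.3.2 and 3.1.3.4 treat as yes/no elements. Taken literally, the composite is yes for essentially all 100 infants, and the ICU-stay element cannot be analysed by the stated test. This rests on two assumptions: that any ICU stay counts as yes, since no other rule is given, and that nearly every infant operated on with bypass has one.

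This is a correctable error in one secondary endpoint. It does not touch the Bayley-IV analysis or the remaining single-element comparisons.

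**What to change.** Remove ICU length of stay from the Table 2 elements that form the yes/no composite, and from the binary per-element and logistic analyses. Analyse it as a duration beside postoperative hospital stay: Pearson's or Spearman's correlation with age at surgery as in section 3.1.3.3, and linear regression as in section 3.1.3.4. A cut-off fixed in advance would also make the item computable, but it would discard information and let the chosen value drive the composite rate.

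The cost is a change to one table entry and a sentence in each of sections 3.1.3.2 to 3.1.3.4, with no new method. One practical check is needed: the data items highlighted in section 2.9 name total and postoperative stay but not ICU stay, so confirm that its duration will be extracted from the medical files.

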### Hypotheses

1.1.

We propose an open-design, observational longitudinal study in which we hypothesize that earlier cardiac surgery may constitute a preoperative neuroprotective strategy and improve the neurodevelopmental outcomes of neonates with complex CHD.

### Main objective

1.2.

The main objective of this study is to assess the correlation between age at surgery (days of life) of neonates with complex CHD and neurodevelopmental outcomes at 24 months, assessed by the scores obtained on the subscales of the Bayley Scale of Infant and Toddler Development®, Fourth Edition® (Bayley-IV test) exploring motor skills, cognition, and language (18).

Our aim is to determine the optimal threshold for the age at surgery that discriminates delayed neurodevelopment / normal neurodevelopment according to the main criterion, i.e. neurodevelopment at 24 months according to the Bayley-IV scale (score <80 vs. ≥80).

### Secondary objectives

1.3.

The secondary objectives of our study are to evaluate the correlation between age at surgery (days of life) of neonates with complex CHD and the following outcomes:
i.the presence and severity of WMIs observed on preoperative and postoperative brain MRI;ii.postoperative morbidity;iii.the duration of the postoperative hospital stay;iv.neurodevelopmental outcomes, including clinical pediatric neurological assessment (4 months, 12 months, and 24 months) and functional motor skill assessment using the Alberta Infant Motor Scale (AIMS; 4 months and 12 months).We will also assess the moderating role of demographic characteristics and pre-, intra-, and postoperative factors on the following outcomes:
i.the frequency of pre-, and postoperative WMIs;ii.postoperative morbidity;iii.neurodevelopmental outcomes, including clinical pediatric neurological assessment (4 months, 12 months, and 24 months), functional motor assessment using the AIMS (4 months and 12 months), and the Bayley-IV test (24 months).

## Methods

2.

### Recruitment

2.1.

Recruitment will be conducted on a prospective cohort (*n *= 100) of neonates with complex CHD requiring cardiac surgery with cardiopulmonary bypass CPB within the first 2 months of life and receiving a pre-operate and postoperative brain MRI, standardized neurological assessments at 4 months, 12 months, and 24 months, and a neuropsychological assessment with a Bayley-IV test at 24 months.

### Inclusion criteria

2.2.

In this study, we will recruit infants aged 2 months or less with complex CHD requiring surgery with extracorporeal circulation during their first 2 months of life at the La Timone Enfants Hospital in Marseille. The included patients should be born full-term (at more than 37 weeks). The eligible complex CHDs correspond to the anatomical classification of Clancy et al. (19), (Table 3).

**Table 3 T3:** Classification of complex congenital heart diseases selected for the study, according to Clancy *et al*. (19).

Classification Number	Anatomic Classification (10)	Complex CHD
I	Two-ventricle heart without arch obstruction	TGA with intact ventricular septum
		TGA/VSD
		Tetralogy of Fallot/PA
		Truncus Arteriosus
		TAPVR
II	Two-ventricle heart with arch obstruction	TGA/VSD/CoAo
		VSD/CoAo
		VSD/Interrupted aortic arch
III	Single-ventricle heart without arch obstruction	Unbalanced AVCD
		Tricuspid atresia
		Mitral atresia
		Heterotaxy
		Double-outlet left ventricle
		Double-outlet right ventricle
		Single ventricle (other)
IV	Single-ventricle heart with arch obstruction	HLHS

PA, Pulmonary Atresia; AVCD, Atrioventricular Canal Defect; VSD, Ventricular Septal Defect; CoAo, Coarctation of the Aorta; HLHS, Hypoplasia of Left Heart Syndrome; TAPVR, Total Anomalous Pulmonary Venous Return; TGA, Transposition of the Great Arteries.

For all patients, we must obtain informed consent from both parents (except in special cases justifying consent from just one parent) or from legal representative(s). The parents or legal representatives must be able to read and speak French. Additionally, the included patients will need to be affiliated with French social security.

### Exclusion criteria

2.3.

Patients will be excluded from this study in cases where they (i) have not received any preoperative or postoperative brain MRI due to their poor state of health, because the parents refused, or for another reason; (ii) have their consent withdrawn.

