### Procedure overview

2.5.

Each recruited patient will participate in the study for 24 months (Figure 1). Following the recruitment (visit 0, V0) conducted in the neonatal period before cardiac surgery, a preoperative brain MRI will be performed before surgery (visit 1, V1) if the health of the neonate allows for this. During the 15 days following the surgery, a postoperative brain MRI is performed (visit 2, V2). Visits 1 and 2 aim to assess preoperative brain injuries and those that appear or worsen postoperatively. The preoperative MRI should not delay cardiac surgery. Visits 3 (V3), 4 (V4), and 5 (V5) will involve neurodevelopmental assessments at 4 months, 12 months, and 24 months, respectively, conducted by a single child neurologist ([name]) and the Alberta Infant Motor Scale (AIMS) assessment at 4 months and 12 months. These assessments will be scheduled and conducted during conventional follow-up cardio-pediatric appointments. During visit 5 (V5), at 24 months, a standardized neuropsychological assessment will be performed using the Bayley-IV test.

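### A missing brain MRI removes a recruited infant from the whole study, so analyses that need no MRI can be selected on severity, timing of surgery and postoperative course

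*Protocol article*

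**What the plan says.** **Where the rule acts.** Section 2.3 opens with "Patients will be excluded from this study in cases where they" and gives as its first ground that they "have not received any preoperative or postoperative brain MRI due to their poor state of health, because the parents refused, or for another reason". The only other ground is withdrawal of consent. Baseline ineligibility is handled separately, in Section 2.4. Recruitment precedes the operation: "Following the recruitment (visit 0, V0) conducted in the neonatal period before cardiac surgery". The rule therefore removes infants who are already in the cohort, and it removes them from the study rather than from one analysis.

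**How the scans come about.** Section 2.1 describes the cohort of 100 as "receiving a pre-operate and postoperative brain MRI". Section 2.5 makes the first scan conditional: "a preoperative brain MRI will be performed before surgery (visit 1, V1) if the health of the neonate allows for this". It adds: "The preoperative MRI should not delay cardiac surgery". The second scan is placed in the 15 days after the operation (Sections 2.5 and 2.6).

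**What needs a scan.** The main objective (Sections 1.2 and 3.1.2) relates age at surgery to Bayley-IV scores at 24 months. AIMS (3.1.2), postoperative morbidity (3.1.3.2) and length of stay (3.1.3.3) are also analysed without imaging. Only Section 3.1.3.1 uses MRI. The article describes no separate analysis set that would keep infants without a scan in the other analyses.

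**The concern.** An exclusion applied after recruitment is harmless only if it is unrelated to exposure and outcome. Here the protocol's own text suggests otherwise, on three counts:

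- **Severity.** Poor health is named in Section 2.3 as a reason for a missing scan.
- **Timing.** Surgery takes priority over the first scan, so a short interval to surgery plausibly means fewer preoperative scans. Age at surgery is the exposure.
- **Postoperative course.** The second scan happens after the exposure. Infants with a complicated recovery are plausibly harder to scan within 15 days. Their complications are the endpoint of Section 3.1.3.2, and the Introduction treats all postoperative morbidities as potential risk factors for brain injury.

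The study wants to derive age thresholds for surgery and to inform guidelines (Introduction and Conclusion). A distorted relation between age and outcome goes straight to that aim. The multivariable models in Section 3.1.3.4 would run on the retained infants only. They cannot bring back those removed, and adjustment does not in general undo selection on an event that follows exposure. If study follow-up stops at exclusion, the 24-month scores cannot be recovered later.

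**Working it through.** **1. The wording.** Two readings of the exclusion are possible.

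| Reading | Supported by | Consequence |
|---|---|---|
| Either scan missing | Section 2.1, which builds both scans into the cohort | An infant whose first scan Section 2.5 allows to be skipped is then excluded by Section 2.3 |
| Both scans missing | Section 2.5, which tolerates an absent first scan | Fewer infants lost, and no conflict with Section 2.5; still a health-related exclusion after recruitment |

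**2. Precision.** Inputs from Section 3.1.1: n = 100, two-sided alpha 5%, power 80%. Detectable correlation by Fisher's z:

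r = tanh[(1.960 + 0.842) / √(n − 3)]

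- The plan's own figure for n = 100 is 0.39. The formula gives tanh(2.802 / √97) = 0.277, and a noncentral t calculation gives 0.272. The stated 0.39 is not reproduced; it corresponds to about 49 infants. That is a separate matter on which this point does not depend.
- The loss to missing MRI is not in the article, so it is assumed: n = 90 gives 0.292, n = 85 gives tanh(2.802 / √82) = 0.300, n = 80 gives 0.309, n = 70 gives 0.330.

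**3. Bias, as an illustration only.** None of these inputs is in the article. With age A, severity S and Bayley score Y all standardised, let Y = −0.2·A − 0.4·S + error, and let a be the correlation of age with severity. Without exclusions the age–Bayley correlation is −0.2 − 0.4·a, that is −0.08, −0.20 and −0.32 for a = −0.3, 0 and +0.3. Infants are then removed for a missing MRI. The probability of loss rises either with severity and earlier surgery equally, or with severity alone. Results from 1,000,000 simulated infants per scenario:

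| a | Loss depends on | All infants | 10% lost | 20% lost | 30% lost |
|---|---|---|---|---|---|
| −0.3 | severity and early surgery | −0.08 | −0.114 | −0.131 | −0.147 |
| −0.3 | severity only | −0.08 | −0.093 | −0.105 | −0.106 |
| 0 | severity and early surgery | −0.20 | −0.232 | −0.245 | −0.256 |
| 0 | severity only | −0.20 | −0.202 | −0.203 | −0.207 |
| +0.3 | severity and early surgery | −0.32 | −0.341 | −0.352 | −0.361 |
| +0.3 | severity only | −0.32 | −0.308 | −0.301 | −0.297 |

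A more negative value favours the hypothesis that earlier surgery is better. In five rows the correlation moves that way, in one of them barely. In the last row it moves against the hypothesis. The sign depends on how severity relates to age and on what drives the loss.

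**The case against.** **A reader might infer that the rule makes early surgery look better.** That follows only if MRI loss is concentrated among sick infants operated on early, and the article does not say so. Its one statement linking severity and timing, in the Introduction, is that low weight or instability can delay surgery. That corresponds to a positive a. With a positive a and loss driven by severity alone, the shift goes against the hypothesis. This objection stands in full: no direction can be claimed.

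**A reader might infer that the rule hides a true disadvantage of early surgery.** Suppose sicker infants are operated on earlier (a = −0.3), severity costs 5 Bayley points per standard deviation, and age has no effect. Splitting at the median age still gives an early-minus-late difference of 2 × 0.798 × 0.3 × (−5) = −2.4 points (0.798 is the mean absolute value of a standard normal variable). That deficit is confounding by severity. If exclusions shrink it, the estimate moves towards the truth. Keeping all infants removes the selection but does not remove confounding.

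**A reader might infer that deaths are lost from the Bayley analysis because of this rule.** An infant who dies before 24 months has no Bayley score under any rule, and Table 2 does not list death as a morbidity. The point concerns survivors without a scan, and non-fatal complications that drop out of the morbidity analysis.

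**The narrower reading of the exclusion.** If only infants with neither scan are excluded, a missing preoperative scan alone excludes nobody. This stands as a limit on the size of the problem, but it does not remove the selection.

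**The study is preliminary, and severity markers are collected.** Both are true (Sections 2.9, 3.1.3.4 and 6). But the primary correlation is unadjusted, and adjusted models still use only retained infants.

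**Conclusion.** The concern holds in a limited form. Section 2.3 applies an imaging requirement to the whole study, although only the white matter analyses need images. Sections 2.3 and 2.5 together tie a missing scan to health, to the priority given to surgery and to the postoperative period. The rule can therefore select the primary Bayley analysis, and the AIMS, morbidity and length-of-stay analyses, on severity, timing and postoperative course.

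The size and sign of the bias are unknown. Under the assumed inputs above, the correlation shifts by between almost nothing and about 0.07 (−0.08 to −0.147), in most scenarios towards the hypothesis and in one against it. The precision cost is minor: about 0.28 to 0.30 in the detectable correlation at an assumed 15% loss. All of this shrinks if the exclusion covers only infants with neither scan, and the article does not settle which reading is meant. The structural defect depends on none of these assumptions.

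**What to change.** 1. Remove ground (i) of Section 2.3 as a study-level exclusion. Withdrawal of consent stays.
2. Keep every consented and operated infant in the Bayley-IV, AIMS, morbidity and length-of-stay analyses.
3. Restrict only the analyses of Section 3.1.3.1 to infants with the scan concerned, preoperative or postoperative.
4. Report how many infants lacked each scan, with the reason, and compare baseline severity and age at surgery between infants with and without it.
5. Reconcile Sections 2.1, 2.3 and 2.5, so that it is clear whether a missing first scan, a missing second scan or only the absence of both has any consequence.

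**Cost.** A short protocol amendment. The MRI and non-MRI analyses will have different denominators, which must be shown. A few more AIMS and Bayley-IV assessments fall to the single child neurologist, at follow-up visits that Section 2.5 already places within conventional cardiology appointments. Perioperative data and complications come from medical files (Section 2.9), so the morbidity and length-of-stay analyses need no extra procedure.
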